**Methods:**

We will collect continuous cardiac waveform data from patients managed in an intensive care unit within a clinical trial. We will first assess the signal quality of the electrocardiogram (ECG) using a combination of the structural image similarity metric and signal quality index. Then, we will detect premature ventricular contractions (PVC) on good-quality ECG beats using a deep-learning model. For arterial blood pressure (ABP) data, we will employ a singular value decomposition (SVD)-based approach to assess the signal quality. Finally, we will compute multiple indices of ANS functions through heart rate turbulence (HRT) analysis, time/frequency-domain analysis of heart rate variability (HRV) and pulse rate variability, and quantification of baroreflex sensitivity (BRS) from high-quality continuous ECG and ABP signals. The early autonomic dysfunction will be characterized by comparing the values of calculated indices with their normal ranges.

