## Statistical analysis

3

The characterization of eAD requires consideration of age-specific analysis. We will stratify patients into age to account for known age-related differences in autonomic function; Within each age stratum, we will establish reference distributions based on published normative data for that specific age group; For each autonomic measure, we will use age-appropriate reference ranges from healthy controls as reported in large-scale studies. Normally, RMSSD values should fall between 19 and 75 ms (48), HRT should exhibit a turbulence onset near 0% and a turbulence slope above 2.5 ms/R-R interval (49), and BRS is around 4.87–34.07 across different age groups over 20 years old (50).

For the determination of eAD, we will quantify the incidence and magnitude of anomalies such as reduced RMSSD, HRT, and BRS, alongside increased low frequency (LF) power and an elevated LF/HF ratio, which are critical indicators. eAD will be characterized if three or more of these indicators exceed or fall below 2.5 standard deviations from age and sex-standardized values. Autonomic function measures will also be considered as continuous variables as well. For the primary analysis, we will use data from patients over their first 24 h following ICU admission to identify eAD, as well as examine the association of these measures with clinical outcomes. In exploratory analysis, we will describe autonomic function measures over the first 5 days following ICU admission.

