## Expected results

4

Quantification of individual eAD indices, defined as reduced RMSSD, reduced HRT, reduced BRS, decreased LF power, decreased LF/HF (45, 51) (less/greater than 2.5 SDs of age/sex-standardized values) measured over 24 h following admission.Quantification of eAD, defined as 3 or more (out of 5) indices less/greater than 2.5 SDs of age/sex-standardized values measured over 24 h following admission.

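### The 2.5 SD rule for early autonomic dysfunction fixes no scale and does not match the plan's own normal ranges, so the classification depends on an unstated choice

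*Protocol article*

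**What the plan says.** The protocol article gives two ways of judging an index abnormal.

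- **Normal ranges.** The abstract (Methods) says that eAD is "characterized by comparing the values of calculated indices with their normal ranges". Section 3 (Statistical analysis) commits to age-appropriate reference ranges for each measure and prints some: "Normally, RMSSD values should fall between 19 and 75 ms" and "BRS is around 4.87–34.07 across different age groups over 20 years old". It also gives a one-sided limit of 2.5 ms per R-R interval for turbulence slope and a value near 0% for turbulence onset.
- **A 2.5 SD rule.** Section 3 continues: "eAD will be characterized if three or more of these indicators exceed or fall below 2.5 standard deviations from age and sex-standardized values". Section 4 (Expected results) repeats it as "Quantification of eAD, defined as 3 or more (out of 5) indices less/greater than 2.5 SDs of age/sex-standardized values", and Section 5 (Discussion) restates it.

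The article gives no mean, SD, distribution shape or transformation for any index. It does not say what proportion of healthy people the printed ranges cover, or which criterion decides. The direction also differs: LF power and LF/HF count when raised in Section 3 and when lowered in Section 4.

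**The concern.** The 3-of-5 count is the variable that the primary analysis uses to identify eAD in the first 24 hours. Three of its five components are reductions under Section 3, and all five are under Section 4, so the position of the lower cut-off largely determines who is classified.

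Two things make that position uncertain. First, a patient can lie outside a printed normal range and yet not be beyond 2.5 SD, and the text does not say which of the two counts. Second, a 2.5 SD distance below the mean has its intended meaning (about 0.6% of healthy values) only if the index is roughly normal on the scale used. For positive, right-skewed quantities such as spectral power, a ratio of powers or a gain, the raw-scale lower cut-off is too low and the upper one is too easily crossed. The reported incidence of eAD would then partly reflect the scale.

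The effect could be sharper in patients with arterial pressure data only. Turbulence is excluded for them, and Section 2.2.6 lists RMSSD, LF/HF and BRS as their metrics. If only those three are counted, all three must be abnormal, and one cut-off that is hard to reach would weigh heavily.

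**Working it through.** The plan states no numeric 2.5 SD cut-off, so there is no figure to reproduce. The check derives the cut-offs that the printed ranges imply.

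**Inputs (Section 3).** RMSSD 19 to 75 ms; BRS 4.87 to 34.07, pooled over age groups; multiplier 2.5. **Assumption:** each range is mean ± k SD. The document does not give k, so it is varied; k = 1.96 (central 95%) is the main reading.

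**1. Raw scale, symmetric reference.** Mean = (L + U)/2; SD = (U − L)/(2k); cut-off = mean − 2.5 SD. At k = 1.96:

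- RMSSD: mean 47.0, SD 28/1.96 = 14.29, cut-off 47.0 − 35.7 = 11.3 ms.
- BRS: mean 19.47, SD 14.60/1.96 = 7.45, cut-off 19.47 − 18.62 = 0.85.

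**2. Log scale.** Centre = √(LU); s = ln(U/L)/(2k); cut-off = centre × exp(−2.5 s). At k = 1.96:

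- RMSSD: centre 37.75, s = 0.350, cut-off 15.7 ms.
- BRS: centre 12.88, s = 0.496, cut-off 3.73.

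**3. Raw-scale rule applied to a right-skewed (lognormal) reference.** Mean = centre × exp(s²/2); SD = mean × √(exp(s²) − 1). At k = 1.96:

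- RMSSD: mean 40.1, SD 14.5, cut-off 3.9 ms. About 4 × 10⁻¹¹ of healthy values lie below it, against Φ(−2.5) = 0.0062 intended. About 2.2% lie above the upper cut-off.
- BRS: mean 14.6, SD 7.7, cut-off −4.7, which a positive index cannot reach. About 2.6% lie above the upper cut-off.

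**4. Sensitivity to k.** Lower cut-offs:

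| Range read as | RMSSD raw, symmetric | RMSSD log | BRS raw, symmetric | BRS log |
|---|---|---|---|---|
| ±1 SD | −23.0 | 6.8 | −17.0 | 1.13 |
| 90% (1.645) | 4.5 | 13.3 | −2.7 | 2.94 |
| 95% (1.96) | 11.3 | 15.7 | 0.85 | 3.73 |
| ±2.5 SD | 19.0 | 19.0 | 4.87 | 4.87 |
| ±3 SD | 23.7 | 21.3 | 7.3 | 5.73 |
| *Printed lower limit* | *19* | *19* | *4.87* | *4.87* |

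With range and cut-off on the same scale, the two criteria coincide only at k = 2.5. At 95%, an RMSSD between 11.3 and 19 ms, or a BRS between 0.85 and 4.87, is outside the printed range but not beyond 2.5 SD on the raw scale. A BRS of 2 is one example.

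**5. General condition.** Mean − 2.5 SD ≤ 0 exactly when SD/mean ≥ 1/2.5 = 0.40. Below that point the tail is already distorted for a lognormal index: with SD/mean 0.2 the healthy proportion below the cut-off is 0.00034, and with 0.3 it is 2.4 × 10⁻⁶, against 0.0062 intended. In the lognormal reading at 95%, SD/mean is 0.36 for RMSSD and 0.53 for the pooled BRS range.

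**The case against.** The strongest reply is that the article states no SD and no scale. Standardised values could already be log-based or centile-based, and such detail is commonly left to an analysis plan. The 2.5 SD rule appears consistently in Sections 3 to 5, the printed ranges can be read as background, and a threshold stricter than a 95% range is a legitimate choice. The size and even the direction of the mismatch depend on k: at ±2.5 SD it vanishes, and at ±3 SD it reverses. The BRS range pools ages, so an SD taken from it may exceed the SD within an age and sex stratum. The measures will also be analysed as continuous variables.

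Much of this stands. The cut-offs above are conditional illustrations, not the plan's figures. A reader might infer that the rule puts lower cut-offs near or below zero in general, so that *reduced* is almost unreachable. The documents do not support that. RMSSD at 95% gives 11.3 ms (symmetric) or 3.9 ms (skewed reference), both positive, and goes below zero only under narrower readings of the range. The tail probabilities describe healthy people, and patients with severe injury may lie much lower. The rule is impossible to meet only where the cut-off is at or below zero. Nor does the argument cover every index: turbulence onset is a signed percentage, the phase-rectified BRS of Equation 8 is a difference that can be negative, and the lower cut-off for LF and LF/HF matters only under Section 4.

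What does not stand is that this is merely deferred detail. The abstract names one criterion and Sections 3 to 5 another, with nothing to rank them. Taken at face value, an SD rule on power, ratio and gain indices also misses its intended tail.

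**Conclusion.** The concern holds in a limited form. The 2.5 SD rule has no stated scale, and it does not agree with the normal-range comparison unless the printed ranges happen to be ±2.5 SD. Under the 95% reading, which is an assumption, the lower cut-offs are about 11.3 ms and 0.85 on the raw scale and 15.7 ms and 3.7 on the log scale, against printed limits of 19 ms and 4.87. The BRS figures rest on a range pooled over ages, and stratum-specific values may be higher.

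That *reduced* could not be met at all follows only where SD/mean is 0.40 or more on the raw scale. This is plausible for the alpha(LF) BRS of Equation 10, LF power and LF/HF. It is not shown for RMSSD, and for LF power and LF/HF the article prints no reference figures to test it. The point should be settled before patients are classified, because it bears directly on the 3-of-5 variable.

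**What to change.** 1. Make one rule decisive for eAD and say so in the abstract and in Sections 3 to 5. Label the printed ranges as descriptive. This step is needed in any case: under the 95% reading, log-scale cut-offs still lie below the printed lower limits.
2. For the strictly positive indices (RMSSD, LF power, LF/HF, alpha(LF) BRS), apply the 2.5 SD cut-off on the natural-log scale within age and sex.
3. For indices that can be zero or negative (turbulence onset, phase-rectified BRS), use the equivalent reference centile where published norms allow: about the 0.6th, or the 99.4th for an upper-tail criterion.
4. Reconcile the direction of LF power and LF/HF between Sections 3 and 4 before fixing which tail counts.

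The cost is wording and a log transform. The drawback is that where a source reports only a mean and SD, the log parameters must be obtained by moments: s² = ln(1 + (SD/mean)²), log-mean = ln(mean) − s²/2. This relies on a lognormal shape and must be stated.

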## Expected results

4

Quantification of individual eAD indices, defined as reduced RMSSD, reduced HRT, reduced BRS, decreased LF power, decreased LF/HF (45, 51) (less/greater than 2.5 SDs of age/sex-standardized values) measured over 24 h following admission.Quantification of eAD, defined as 3 or more (out of 5) indices less/greater than 2.5 SDs of age/sex-standardized values measured over 24 h following admission.

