### Data analysis

2.2

Based on data from the currently recruited 550 patients, we found some incomplete ECG recordings of short duration, necessitating data analysis based solely on the ABP signal. To address this issue, we will conduct the eAD characterization on two fronts: one from both ECG and ABP waveforms, and the other from only ABP waveforms.

We will conduct non-invasive characterization of eAD by computing multiple indices over 24 h following admission, including heart rate turbulence (HRT) (18), time- and frequency-domain analyses of HRV and sequence analysis of BRS. First, we will slice the long-monitoring waveform into 1-h segments and assess the signal quality for both ECG and ABP segments. Next, the premature ventricular contractions (PVC) detection will analyze high-quality ECG segments. If more than 10 PVC beats for a given 1-h segment are detected, we will conduct HRT analysis on ECG waveforms (19). HRT is generally assessed by two parameters: turbulence onset (TO) and turbulence slope (TS). TO measures the initial acceleration and subsequent deceleration of heart rate after a PVC, while TS quantifies the rate of heart rate return to baseline. We will extract two time series from the ECG and ABP waveforms: one consisting of RR intervals from normal sinus beats, and the other comprising systolic blood pressures (sBP) from ABP pulses. We will then perform three analyses on these sequences: extracting root mean square of successive differences (RMSSD) and HRT from time-domain RR interval sequences, transforming RR intervals into the frequency domain to calculate the low- and high-frequency band ratio, and estimating BRS indices from RR intervals and sBP sequences. For eAD characterization based on ABP signals alone, we will compute autonomic indices from pulse interval sequences, excluding HRT due to the difficulty of detecting PVC beats without ECG waveforms. Figure 1 summarizes the entire procedure, with detailed explanations of each function block provided in the following sections.

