For the case of eAD characterization utilizing ABP signal alone, we will extract pulse-to-pulse interval (PPI) based on detected systolic blood pressure from high-quality ABP waveforms and calculate pulse rate variability. We identify the intervals between fiducial points in successive pulses as PPI. Based on PPI time series, we will calculate RMSSD, the ratio of LF/HF and BRS metrics in place of using RR interval time series.

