## Discussion

5

This study’s novelty lies not in the development of new autonomic measures, but rather in three key aspects: (1) the first application of HRT analysis in sTBI patients, providing new insights into post-ectopic beat autonomic regulation in this population; (2) the comprehensive integration of multiple autonomic measures in a large cohort of sTBI patients, allowing for robust characterization of autonomic dysfunction patterns specific to this population; and (3) the potential to establish normative values and clinical thresholds for autonomic measures in acute sTBI, which are currently lacking. This approach will provide clinicians with a more complete understanding of autonomic dysfunction in sTBI and its relationship to clinical outcomes.

Following sTBI, eAD is a complex and multifaceted issue that can significantly impact a patient’s overall health and recovery. Characterizing eAD is crucial for risk assessment, customizing pharmacological interventions, and assessing rehabilitation strategies. While small studies indicate that eAD is associated with poor outcomes following sTBI, the duration and full trajectory of eAD has been poorly characterized. This protocol outlines the data analysis procedure for quantifying acute autonomic dysfunction using cardiac telemetry waveforms. We will collect and annotate waveform data from 550 patients in a clinical trial and quantify the incidence and magnitude of eAD indices after the first day of admission. We will characterize eAD as the presence of 3 or more indices less/greater than 2.5 SDs of age/sex-standardized values measured over 24 h following admission.

In some patients, simultaneous ECG and ABP signals may be unavailable. To solve this problem, we will divide the collected data into subgroups with and without ECG information and examine eAD within both subgroups. We will report results of the planned study in one or multiple scientific papers in international peer-reviewed journals. We will note and deviations from this protocol, if any occur, in these publications.

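### The fixed three-of-five eAD rule is applied to patients in whom HRT cannot be computed, so eAD incidence depends partly on PVC count and signal availability as well as on autonomic function

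*Protocol article*

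**What the plan says.** The Expected results section lists five indices ("reduced RMSSD, reduced HRT, reduced BRS, decreased LF power, decreased LF/HF") and has eAD "defined as 3 or more (out of 5) indices less/greater than 2.5 SDs of age/sex-standardized values". The Statistical analysis section uses the same fixed count: "eAD will be characterized if three or more of these indicators exceed or fall below 2.5 standard deviations". The Discussion repeats it. The Statistical analysis section places eAD, identified over the first 24 h, in the primary analysis, together with the association of these measures with clinical outcomes.

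Two rules decide whether HRT exists for a patient, both in the Data analysis section:

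- With ECG: "If more than 10 PVC beats for a given 1-h segment are detected, we will conduct HRT analysis on ECG waveforms". The section on heart rate turbulence quantification also requires two sinus RR intervals before the coupling interval and 15 RR intervals after the compensatory interval.
- With ABP only, indices come from pulse intervals, "excluding HRT due to the difficulty of detecting PVC beats without ECG waveforms".

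For ABP-only data, the section on heart/pulse rate variability states that "we will calculate RMSSD, the ratio of LF/HF and BRS metrics in place of using RR interval time series". The Discussion adds that "we will divide the collected data into subgroups with and without ECG information and examine eAD within both subgroups".

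Nowhere does the article change the threshold, require a minimum number of computable indices, or say how an uncomputed HRT is scored.

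**The concern.** A threshold of three is stricter when fewer indices can be measured. Take two patients with the same two abnormal results among RMSSD, BRS, LF power and LF/HF, and the same impaired turbulence response. The one with a qualifying hour of PVCs reaches three and is labelled eAD. The other, with too few PVCs or no usable ECG, stays at two and is not.

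Two things are at stake. First, an eAD incidence from patients with HRT and one from patients without it are not on the same scale. Secondly, within the ECG group PVC count decides whether a patient has five or four chances to reach three. If PVC frequency is itself related to outcome, that relation could carry into the eAD-outcome association.

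**Working it through.** **Inputs from the article.** The threshold is 3. The stated denominator is 5, and counting the listed indices reproduces it. The article states no eAD incidence, so there is no further figure to reproduce.

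**Indices available per patient.** LF power appears as an index only in the Statistical analysis and Expected results sections. The descriptions of both the ECG branch and the ABP-only branch name only the LF/HF ratio as spectral output. Treating the branches alike gives two readings:

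| Data situation | LF power counted in both branches | LF power counted in neither |
|---|---|---|
| ECG and ABP, HRT computed | 5 | 4 |
| ECG and ABP, HRT not computed | 4 | 3 |
| ABP only | 4 | 3 |

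LF/HF cannot be formed without LF power, so the first reading is the natural one.

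**Direction.** At a fixed threshold, adding an index can leave the count unchanged or raise it, never lower it. Fewer computable indices therefore cannot raise the chance of an eAD label, whatever the probabilities.

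**Size (assumption).** Let each index be abnormal with the same probability p. Neither p nor the correlation between indices is in the article, so ranges are shown. With independent indices:

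- P(at least 3 of 5) = 10p³(1−p)² + 5p⁴(1−p) + p⁵
- P(at least 3 of 4) = 4p³(1−p) + p⁴
- P(3 of 3) = p³

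At p = 0.3:

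- Five indices: 0.1323 + 0.02835 + 0.00243 = 0.16308
- Four indices: 0.0756 + 0.0081 = 0.0837
- Three indices: 0.027

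The gap between five and four equals the chance of exactly two abnormal among four, times p: 6p²(1−p)² × p = 6 × 0.09 × 0.49 × 0.3 = 0.0794. That agrees with 0.1631 − 0.0837.

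The correlated cases use a common-factor normal model with 1,000,000 draws each.

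| Correlation | p | 5 indices | 4 indices | 3 indices | Ratio 5 to 4 | Ratio 4 to 3 |
|---|---|---|---|---|---|---|
| 0 | 0.1 | 0.9% | 0.4% | 0.1% | 2.3 | 3.7 |
| 0 | 0.3 | 16.3% | 8.4% | 2.7% | 1.9 | 3.1 |
| 0 | 0.5 | 50.0% | 31.3% | 12.5% | 1.6 | 2.5 |
| 0 | 0.7 | 83.7% | 65.2% | 34.3% | 1.3 | 1.9 |
| 0.3 | 0.3 | 22.9% | 14.9% | 6.7% | 1.5 | 2.2 |
| 0.6 | 0.3 | 26.8% | 20.5% | 12.1% | 1.3 | 1.7 |
| 0.8 | 0.5 | 50.1% | 44.4% | 34.6% | 1.1 | 1.3 |

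Ratios are taken from the unrounded results.

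**Mixing within the ECG group.** If a share q of ECG patients has HRT, incidence at p = 0.3 with independent indices is q × 16.3% + (1−q) × 8.4%. This is 9.2% at q = 0.1 and 15.5% at q = 0.9, with physiology unchanged. The article does not give q.

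**The hourly gate.** Ten PVCs in each of 24 hours is 240 PVCs, and no hour exceeds 10, so HRT is not computed. Eleven PVCs in one hour is enough to compute it, although the indices are described as measured over 24 h.

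**The case against.** The strongest defence has four parts.

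1. The groups with and without ECG are to be examined separately, and the article proposes no pooled or head-to-head incidence. This limits mixing across signals. It does not make the two incidences comparable, and it leaves HRT availability within the ECG group untouched.
2. The article does not say that an uncomputed HRT counts as normal; such a patient might be treated as not evaluable, and an analysis plan that is not shown might settle this. That is fair as far as it goes. But under the stated rule an absent index cannot contribute to three. Classifying only patients with all five would remove every ABP-only patient, in whom the Discussion says eAD will be examined.
3. The individual indices and the continuous measures are also analysed, and these do not depend on the count. This stands, and it confines the problem to the eAD classification and its association with outcome.
4. The hourly PVC minimum rests on a cited source that is not at hand, and how often the 240-against-11 case occurs is unknown. Changing the gate is therefore optional.

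A reader might also infer a contrast of five indices against three, with incidences differing about sixfold (16.3% against 2.7% at p = 0.3). The documents do not support this. It would require crediting LF power to the ECG branch and denying it to the ABP-only branch, when neither description names it as an output.

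**Conclusion.** The point holds. A fixed count of three is applied across patients who differ in how many indices can exist, and nothing in the article corrects for it. Counting LF power in both branches, the comparison is five indices against four, and the ratio of eAD probabilities is about 1.1 to 2.3 over p = 0.1 to 0.7 with independence and the correlated cases run. If LF power is counted in neither branch, it is four against three, for example 8.4% against 2.7% at p = 0.3. The direction needs no assumption; the sizes rest on assumed equal probabilities and assumed correlations. The share of patients lacking HRT is not stated, so the size of the bias in this cohort cannot be given.

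Two stronger conclusions might be drawn and should not be. One is that eAD incidence reflects data availability instead of autonomic function. It reflects both: with four independent indices it runs from 0.4% at p = 0.1 to 65.2% at p = 0.7. The other is that patients with frequent PVCs are sicker, so that an outcome association is built in. The article gives no evidence for that; it is only a possibility.

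**What to change.** 1. First reconcile the abnormal direction of LF power and LF/HF. The Statistical analysis section treats increases as abnormal and the Expected results section treats decreases as abnormal. Until this is settled, two of the four core indices have no usable definition.
2. Define primary eAD on the indices obtainable in every patient: RMSSD, BRS, LF power and LF/HF. Make LF power an explicit output in both branches.
3. State one cut-off for this set, for example keeping three or more, now of four.
4. Report HRT as a separate index. Report the five-index composite as a secondary analysis, only in patients with all five, and also show eAD by number of available indices.
5. Optionally, apply the minimum PVC count to eligible PVCs pooled over the 24 h instead of hour by hour.

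With a common set, equal per-index probabilities and correlations give equal incidence whatever the PVC count or signal: at p = 0.3 with independence, 8.4% for everyone under three of four. The cost is a change of wording before patients are classified. The downside is that HRT, which the Discussion presents as the first novelty of the study, leaves the primary composite, although it is still reported.
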